### Statistical aspects

#### Sample size calculation

The DIPLOMA-2 trial is designed as a non-inferiority trial, hypothesizing that the mean CCI® score of MIPD is non-inferior to OPD. Calculations are based on results of the pan-European E-MIPS retrospective cohort study and on individual patient-data collected from the previous conducted RCTs on MIPD versus OPD. The sample size is calculated using PASS 2022 software to achieve 80% power (1-β) in a per-protocol analysis with the following assumptions: 2.5% one-sided significance level (α), expected difference of the mean CCI® score in the MIPD and OPD group of 0 points, and a non-inferiority margin of 7.5 points, standard deviation of 20 points in both groups, including 5% metastasized disease, a 10% conversion rate and a 3% lost-to-follow-up rate after randomization leads to a total number of patients to be randomized of 288 (192 in the MIPD study arm and 96 in the OPD study arm). For time to functional recovery, we assume MIPD will result in a reduction of 2 days (7 days in the MIPD group versus 9 days in the OPD group. Time to functional recovery will be measured in days and will be tested for superiority using the Wilcoxon (Gehan-Breslow) test or the log-rank test (based on non-normal distribution). With a one-sided testing, assuming 5% metastatic disease, 10% conversion rate, and 3% loss to follow-up, a sample of 247 patients (159 in the MIPD group and 88 in the OPD group) in a per protocol analysis achieves 80% power to detect a 28% reduction of time to functional recovery (i.e., 6.5 days in the MIPD group; hazard ratio = 0.72). The estimated median time to functional recovery of 9 days in the OPD group is based on results of the LEOPARD-2 trial and corresponds to a median TTFR reduction of 2.5 days.

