## Discussion

The DIPLOMA-2 trial is an international randomized controlled, patient-blinded trial assessing the non-inferiority of MIPD compared to OPD regarding overall complications in patients with any pancreatic and peri-ampullary neoplasm. The study was carefully designed and initiated by the European Consortium on Minimally Invasive Pancreatic Surgery (E-MIPS), to ensure the generating of high-quality data that can be used to guide clinical practice and improve patient outcomes. The DIPLOMA-2 trial will represent a significant advancement in the field of pancreatic surgery, as it is the first international multicenter patient-blinded randomized controlled trial comparing MIPD with OPD for premalignant and malignant disease.

To date, four randomized studies on L-MIPD versus OPD have been published, of which two single center studies, and two multicenter studies [4–7]. Three studies reported that LPD was safe and feasible, with lower blood loss, shorter hospital stay, and faster recovery with similar mortality and mortality, as compared to OPD. However, the LEOPARD-2 trial was terminated early because of a trend towards higher mortality rate in the L-MIPD group (5 (10%) vs 1 (2%), *P* = 0.20) which raised questions regarding the safety of this approach. This led to a reduction in the use of L-MIPD worldwide and ever since the question of the safety of MIPD versus OPD remained a topic of debate [41]. For this reason, the E-MIPS consortium collectively decided that in order to safely and validly expand MIPD worldwide, a new large international multicenter trial in experienced high-volume centers with strict quality standards was needed, with the necessary modifications to the design.

For this reason, the primary outcome of the DIPLOMA-2 trial is overall complications, measured using the CCI®. This choice was based on the various (online) meetings with all principal investigators involved, where there was consensus on safety as the most clinically relevant endpoint for patients undergoing MIPD. By focusing on cumulative complications, the trial aims to capture a comprehensive picture of the safety and efficacy of MIPD compared to OPD. Because the expected benefits of MIS lie in the reduction of surgical impact, and therefore enhanced postoperative recovery, the trial is also powered to assess superiority of time to functional recovery, as a most important second outcome measure.

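### Time to functional recovery: the plan assumes a 2-day gain (7 versus 9 days), but its 80% power belongs to a 2.5-day gain (6.5 versus 9 days), and no power is given for the assumed effect

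*Protocol article*

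**What the plan says.** All the planning figures for time to functional recovery stand in one paragraph of the protocol article, under Sample size calculation.

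- The assumption: "we assume MIPD will result in a reduction of 2 days (7 days in the MIPD group versus 9 days in the OPD group".
- The sample: "a sample of 247 patients (159 in the MIPD group and 88 in the OPD group", described as per-protocol and tested one-sided, with no significance level given.
- The power: "80% power to detect a 28% reduction of time to functional recovery (i.e., 6.5 days in the MIPD group; hazard ratio = 0.72".
- The same effect in days: it "corresponds to a median TTFR reduction of 2.5 days".
- The control value: "The estimated median time to functional recovery of 9 days in the OPD group is based on results of the LEOPARD-2 trial".

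The Discussion then says that "the trial is also powered to assess superiority of time to functional recovery", and the Conclusion repeats the claim. Neither names the effect to which it applies. The test is to be either the Gehan-Breslow Wilcoxon or the log-rank test. The Statistical analysis section sets a general two-tailed threshold of 0.05.

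**The concern.** Two days out of nine is 22%; two and a half out of nine is 28%. Rounding cannot explain the difference, because 7 and 6.5 days, and 2 and 2.5 days, are all printed. The 80% goes with the larger effect only, and the article gives no power for the effect it says it assumes.

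This outcome carries the superiority half of the trial's hypothesis. A reader of the Discussion and Conclusion would take it that a true 2-day gain has an 80% chance of being detected. If the chance is nearer 60% or 47%, a non-significant result is weak evidence against a 2-day benefit and could be misread as strong evidence.

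Two lesser points affect how the 80% is read: the one-sided level is missing, and the hazard ratio has no stated direction although the event is a favourable one.

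**Working it through.** **Inputs from Sample size calculation.** Medians 9 days (OPD) and 6.5 or 7 days (MIPD); hazard ratio 0.72; 159 + 88 = 247 patients. The 247 follows from the 288 randomized with the stated losses, conversion applying to MIPD only: 192 × 0.95 × 0.90 × 0.97 = 159.2 and 96 × 0.95 × 0.97 = 88.5.

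**Assumptions.**
- All 247 patients recover, so there are 247 events. No event count is stated, and this is the most favourable case for that sample.
- The hazard ratio equals the ratio of medians (exponential times). The article does this itself when it pairs 28% with 0.72.
- One-sided level 5% or 2.5%. The first is inferred. The second is the level stated for the primary outcome, and for a benefit in the expected direction it is equivalent to two-tailed 0.05.

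**Formula (Schoenfeld).** Power = Φ(|ln HR| × √(D·p·(1−p)) − z_α), with D = 247 and p = 159/247 = 0.6437. The root is √(247 × 0.6437 × 0.3563) = 7.527.

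**Step 1: reproduce the stated 80%.** |ln 0.72| = 0.3285, and 0.3285 × 7.527 = 2.473.
- One-sided 5%: Φ(2.473 − 1.645) = Φ(0.828) = 79.6%.
- One-sided 2.5%: Φ(2.473 − 1.960) = Φ(0.513) = 69.6%.

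The unrounded ratio 6.5/9 gives 78.9% and 68.8%. So the stated figure is met at one-sided 5% and not at 2.5%.

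**Step 2: the assumed effect.** |ln(7/9)| = 0.2513, and 0.2513 × 7.527 = 1.892.
- One-sided 5%: Φ(1.892 − 1.645) = Φ(0.247) = 59.7%.
- One-sided 2.5%: Φ(1.892 − 1.960) = Φ(−0.068) = 47.3%.

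| Effect | Ratio of medians | Power, one-sided 5% | Power, one-sided 2.5% |
|---|---|---|---|
| 6.5 v 9 days (HR 0.72) | 0.72 | 79.6% | 69.6% |
| 7 v 9 days | 0.778 | 59.7% | 47.3% |

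**Step 3: other sample and test.**
- If all 288 randomized patients recover (2:1), the root is √(288 × 2/9) = 8, and 8 × 0.2513 = 2.011. Power for 7 versus 9 days is 64.3% (5%) and 52.0% (2.5%).
- Simulation with exponential times and 159/88 patients, 7 versus 9 days, one-sided 5%: log-rank 59.2%, Wilcoxon 50.4%.
- Recoveries needed for 80% power at 7/9 and this allocation: 6.183/(0.2513² × 0.2294) = 427 at one-sided 5%, and 7.849/(0.2513² × 0.2294) = 542 at 2.5%.

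**Step 4: other distribution shapes.** With Weibull times of shape k, the log hazard ratio is multiplied by k for both effects. In log-rank simulations at one-sided 5%:

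| Shape | 7 v 9 days | 6.5 v 9 days |
|---|---|---|
| 1 | 59.2% | 78.0% |
| 1.25 | 75.1% | 90.8% |
| 1.5 | 88.2% | 97.4% |

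The two powers rise together. If the 80% for 6.5 versus 9 days is held fixed, the power for 7 versus 9 days follows whatever the shape. The log ratios stand as 0.2513/0.3254 = 0.772.
- At 5%: 0.772 × (1.645 + 0.842) − 1.645 = 0.275, power 61%.
- At 2.5%: 0.772 × (1.960 + 0.842) − 1.960 = 0.204, power 58%.

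Reaching 80% at 2.5% would need k = 2.802/2.449 = 1.14. The hazard ratio would then be (6.5/9)^1.14 = 0.69, not the printed 0.72.

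**The case against.** The strongest defence is that the paragraph gives an expected effect and then a detectable one. The 288 patients are fixed by the complication index; the later sentences say what the resulting per-protocol sample can detect, and they name that effect openly. This stands in part: the power sentence is not miscalculated for the effect it names. But the text does not label the two effects in that way, and the reading still leaves the expected effect without a power.

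A reader might infer that 60% is the most the trial can achieve for a 2-day gain. The documents do not support that. The figure rests on exponential times and on 247 patients. It is about 64% if all 288 recover, and higher for Weibull shapes above 1. The modified intention-to-treat set, not the per-protocol set, is the primary analysis set, although the converted patients it keeps may dilute the effect. What remains is that shapes which lift the 60% also move the stated 80%, or contradict the printed hazard ratio.

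A reader might also infer that a hazard ratio of 0.72 describes slower recovery after MIPD. The article does not say which arm is the numerator. Read as OPD to MIPD, 0.72 agrees with faster recovery after MIPD, and the Schoenfeld power is the same either way. It is a labelling gap.

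Finally, this is a secondary outcome, 269 of 288 patients were already randomized at submission (Trial status), and a detailed analysis plan is promised before database lock. That limits the consequence. It does not reconcile two printed figures.

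**Conclusion.** The point holds as an unreconciled planning effect. The article assumes 7 versus 9 days and claims 80% power for 6.5 versus 9 days. Under its own convention, power for the assumed effect is about 60% at one-sided 5% and about 47% at one-sided 2.5%, so the chance of missing a true 2-day gain is about 40% to 53%. The general claim in the Discussion and Conclusion that the trial is powered for this outcome is supported only for the 2.5-day effect, and then only at an inferred one-sided 5%. At one-sided 2.5%, or the two-tailed 0.05 of the Statistical analysis section, that effect has about 70%.

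The exact percentages rest on exponential times, 159/88 patients and recovery in all of them. The contradiction between the two effects rests on the text alone. The primary non-inferiority comparison is not touched.

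**What to change.** In Sample size calculation, and in the statistical analysis plan before database lock:

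1. Label 7 versus 9 days (22%) as the expected effect and 6.5 versus 9 days (28%) as the effect detectable with about 80% power.
2. State the one-sided level for this outcome and align it with the two-tailed 0.05 in Statistical analysis.
3. Report power for both effects at that level: about 80% and 60% at one-sided 5%, or about 70% and 47% at one-sided 2.5%. Name the distributional assumption and the number of recoveries.
4. Give the hazard ratio a direction: hazard of recovery, MIPD to OPD, 9/6.5 = 1.38 and 9/7 = 1.29.
5. In the Discussion and Conclusion, make the statements that the trial is powered conditional on the 2.5-day effect.

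Simply replacing the 2-day assumption by 2.5 days is not advised. With 93% of patients randomized, it would fit the assumption to the power and hide the gap.

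The cost is wording and a less favourable stated power for a secondary outcome. No extra patients and no change of analysis are needed.

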The primary outcome measure “CCI®” will be expressed as means (standard deviations) or medians (interquartile ranges) and will be tested for non-inferiority using independent samples *t*-test or Mann–Whitney *U* test, as appropriate dependent of the distribution. The most important secondary outcome measure “time to functional recovery” will be measured in days and will be tested for superiority using the Wilcoxon (Gehan-Breslow) test or log-rank test, depending on the distribution. Secondary analysis will include correction for censored patients (death before time to functional recovery obtained). For the primary study outcome, the lower limit of the two-sided 95% confidence interval of the difference in proportions will be reported and compared with the non-inferiority margin. Additionally, the individual functional recovery criteria will be analyzed separately. Major complications, expressed in proportions, will be tested for non-inferiority using chi-square or Fisher’s exact test as appropriate. The distribution of variables will be determined using several plots (boxplot, Q-Q plot and histogram) and the Kolmogorov–Smirnov and Shapiro–Wilk tests. For comparison of normally distributed continuous variables, the independent samples *t*-test will be used, and values will be expressed as means (standard deviations). Continuous non-normally distributed variables will be compared using the Mann–Whitney *U* test, and values will be expressed as medians (interquartile ranges). Categorical variables will be compared by chi-square or Fisher’s exact test as appropriate, and values will be expressed as proportions. A two-tailed *p*-value < 0.05 will be considered statistically significant. Time to event endpoints, such as survival, will be calculated using Kaplan–Meier estimations. A Cox regression analysis will be performed to investigate predictors of postoperative survival. All parameters with a *p*-value < 0.1 in a univariable analysis will be included in the multivariable Cox regression analysis. Additionally, multivariable analyses will be performed to determine predictors for primary and secondary study outcomes, for example the occurrence of major complications, postoperative pancreatic fistula, and R0 resection. Furthermore, predictors for receiving adjuvant chemotherapy or readmission will be assessed.

For subjects who are lost to follow-up, a sensitivity analysis will be performed to determine best case/worst case scenarios.

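### The single 80% power figure for time to functional recovery fits only the log-rank test at an unstated one-sided 5% level, yet the plan also permits Gehan-Breslow

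*Protocol article*

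**What the plan says.** In the protocol article, the Sample size calculation section says that time to functional recovery "will be tested for superiority using the Wilcoxon (Gehan-Breslow) test or the log-rank test (based on non-normal distribution". The Statistical analysis section repeats the pair: the outcome is to be "tested for superiority using the Wilcoxon (Gehan-Breslow) test or log-rank test, depending on the distribution".

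Only one power figure follows. It is introduced by "With a one-sided testing, assuming 5% metastatic disease, 10% conversion rate, and 3% loss to follow-up", and the claim is that "a sample of 247 patients (159 in the MIPD group and 88 in the OPD group") in a per-protocol analysis "achieves 80% power to detect a 28% reduction of time to functional recovery". The reduction is translated into medians of 6.5 and 9 days and a hazard ratio of 0.72. The sentence names neither the test that the 80% refers to nor a significance level.

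Two levels appear elsewhere. The primary outcome is planned with a "2.5% one-sided significance level (α), expected difference of the mean CCI® score in the MIPD and OPD group of 0 points". The general rule in the Statistical analysis section is "A two-tailed *p*-value < 0.05 will be considered statistically significant". The Discussion and the Conclusion both describe the trial as powered for superiority on this outcome.

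**The concern.** Log-rank and Gehan-Breslow weight the data differently. Log-rank treats every recovery time alike, whereas Gehan-Breslow weights each time by the number still at risk, so later recoveries count for less. When the effect is one constant hazard ratio, as the planning figure implies, log-rank is the efficient choice and Gehan-Breslow loses power. One power value therefore cannot describe both permitted tests under that effect.

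The missing error level adds to this, because the same sample and effect give clearly different power at one-sided 5% and at two-sided 5%.

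The article relies on the trial being powered for its leading secondary outcome. If the actual power is nearer two thirds or lower, a non-significant result says less against a recovery benefit than the published 80% suggests.

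**Working it through.** **Inputs from the Sample size calculation section.** 192 and 96 randomised; losses of 5% (metastatic disease), 10% (conversion) and 3% (follow-up); 159 and 88 analysed; hazard ratio 0.72; medians 6.5 and 9 days.

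**Assumptions.** The article gives no censoring rate, so all 247 patients are taken to reach recovery. The error level is also not given, so one-sided 5% and two-sided 5% (one-sided 2.5%) are both tried.

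**Step 1: arm sizes.** 192 × 0.95 × 0.90 × 0.97 = 159.2 and 96 × 0.95 × 0.97 = 88.5. These agree with 159 and 88.

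**Step 2: planning model.** 6.5 / 9 = 0.722. A ratio of medians equals a ratio of hazards when times are exponential, so the stated 0.72 fits a constant-hazard model.

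**Step 3: log-rank (Schoenfeld).** Allocation fractions are 159/247 = 0.644 and 88/247 = 0.356.

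z = √(247 × 0.644 × 0.356) × ln(1/0.72) = 7.53 × 0.3285 = 2.47

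- One-sided 5%: Φ(2.47 − 1.645) = 79.6%. The stated 80% reproduces.
- Two-sided 5%: Φ(2.47 − 1.96) = 69.6%. It does not.

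Freedman's formula gives 82.3% or 75.7% at one-sided 5%, depending on the direction of the ratio, and 72.9% or 64.8% at one-sided 2.5%. Again only the 5% level brackets 80%.

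**Step 4: Gehan-Breslow.** Without censoring its weight is proportional to the survival function S. Under proportional hazards its efficiency relative to log-rank is (∫S dF)² / ∫S² dF = (1/2)² / (1/3) = 0.75.

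z = 2.47 × √0.75 = 2.14

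- One-sided 5%: Φ(2.14 − 1.645) = 69.0%.
- Two-sided 5%: Φ(2.14 − 1.96) = 57.2%.

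As a cross-check, with no censoring Gehan-Breslow is the Mann-Whitney test, with P = 1/(1 + 0.72) = 0.581. Its power formula gives 68.2-68.7% at one-sided 5% and about 56% at one-sided 2.5%.

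**Step 5: simulation.** Exponential times, 159 and 88 patients, 8,000 trials per row:

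| Scenario | Log-rank, one-sided 5% | Gehan-Breslow, one-sided 5% | Log-rank, one-sided 2.5% | Gehan-Breslow, one-sided 2.5% |
|---|---|---|---|---|
| All recoveries observed | 79.4% | 67.6% | 68.4% | 55.7% |
| Times rounded up to whole days | 78.0% | 67.8% | 67.8% | 55.3% |
| 5% random censoring | 78.3% | 66.8% | 68.1% | 54.8% |
| Observation cut at 30 days | 76.2% | 67.3% | 65.3% | 54.7% |

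With no effect, both tests rejected at close to the nominal rate (4.7% and 5.0% at the 5% level).

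**Step 6: recoveries needed for 80% power.** At one-sided 5%: 250 for log-rank and 250 / 0.75 = 333 for Gehan-Breslow. At one-sided 2.5%: 318 and 424.

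**Step 7: dependence on the model.** Keeping the medians and arm sizes at one-sided 5% but changing the shape of the distribution (the shapes are assumptions, not from the article):

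| Distribution | Gehan-Breslow | Log-rank |
|---|---|---|
| Log-normal, sigma 0.9 | 84% | 79% |
| Log-normal, sigma 1.0 | 77-79% | 72-73% |
| Log-logistic, scale 0.6 | 77% | 66% |
| Weibull, shape 1.2 | 82% | 90% |

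**The case against.** The strongest reply is that the article never attaches the 80% to Gehan-Breslow. Two tests joined by an or have no order of priority. The figure may simply have been calculated for log-rank, with Gehan-Breslow held back for data in which hazards are not proportional, and there the efficiency loss in Step 4 would not apply. The detailed statistical analysis plan, promised before database lock, could settle the rule.

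Much of this stands. A reader might infer that Gehan-Breslow is the planned test because it comes first, that it is always the weaker test, or that 67-69% is the trial's real power. The documents support none of these. Step 7 shows that Gehan-Breslow can do better under other distributions with the same medians. The 247 is also a per-protocol count, while the main analysis set is modified intention-to-treat, so these percentages test the published power statement and do not give the power of the final main analysis.

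Two things remain. The only effect model that the article commits to is a single hazard ratio of 0.72, and under it the two permitted tests do not share one power. And even if the 80% is read as log-rank alone, it needs a one-sided 5% level that the article does not state and that differs from both levels it does state. Choosing the test later would not correct either feature of the published figure.

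**Conclusion.** The point holds in a conditional form. With a constant hazard ratio of 0.72, 159 and 88 patients and nearly all recoveries observed, the published 80% is a log-rank figure at one-sided 5%. Gehan-Breslow then has about 67-69%, some 10 to 13 points less. At the article's two-tailed 0.05 rule the values are about 67-70% for log-rank (65% if observation stops at 30 days) and 54-57% for Gehan-Breslow. So naming log-rank does not by itself justify 80%. The unstated error level costs about as much power as the choice of test.

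The one-sided 5% level is inferred from the fact that the figure reproduces there. The Gehan-Breslow shortfall depends on proportional hazards. It would be too strong to say that the test is unsuitable or that the trial is underpowered whatever the distribution of recovery times. The point concerns the planned power of a secondary outcome and does not touch the primary outcome.

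**What to change.** In the Sample size calculation and Statistical analysis sections (or in the statistical analysis plan before database lock):

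- Replace the distribution-dependent choice with log-rank as the single superiority test for time to functional recovery, because it matches the stated hazard ratio.
- State the error level and sidedness for this outcome.
- Restate the power at that level: about 80% only at one-sided 5%, about 70% at two-sided 5%.
- If Gehan-Breslow is kept instead, give its power under the stated hazard ratio: about 67-69% at one-sided 5% or 54-57% at two-sided 5%.

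The cost is a few sentences and no extra patients. The downside is that log-rank gives less weight to early differences, which may be where a recovery benefit appears, and that the stated power may become less favourable.

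### The 80% power claimed for time to functional recovery matches a one-sided 5% level; at the plan's own two-tailed 0.05 threshold it is about 70%

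*Protocol article*

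**What the plan says.** The Sample size calculation section of the protocol article contains two calculations.

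- **Primary outcome (CCI).** The level is explicit: "2.5% one-sided significance level (α), expected difference of the mean CCI® score in the MIPD and OPD group of 0 points".
- **Time to functional recovery.** The test is for superiority, by Gehan-Breslow or log-rank. The basis is "With a one-sided testing, assuming 5% metastatic disease, 10% conversion rate, and 3% loss to follow-up, a sample of 247 patients", and the sample "achieves 80% power to detect a 28% reduction of time to functional recovery (i.e., 6.5 days in the MIPD group; hazard ratio = 0.72"). The test is called one-sided, but no level is attached to it.

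The Statistical analysis section describes the recovery test and later sets a single threshold: "A two-tailed *p*-value < 0.05 will be considered statistically significant". It makes no exception for time to functional recovery. The Discussion and the Conclusion both say that the trial is powered for superiority on this outcome.

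**The concern.** A two-tailed 0.05 rule spends 2.5% in the direction of benefit. If the 80% power was computed at one-sided 5%, the design and the decision rule use different levels for the same test. A result with a one-sided p between 0.025 and 0.05 would then count as superior under the power calculation and as non-significant under the analysis section.

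Faster recovery is half of the trial's stated hypothesis, so this affects a headline claim. The mismatch does not depend on the choice of analysis set, because it already appears in the per-protocol set on which the calculation was made.

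**Working it through.** **Inputs, all from the Sample size calculation section**

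- Randomized: "288 (192 in the MIPD study arm and 96 in the OPD study arm").
- Attrition: "assuming 5% metastatic disease, 10% conversion rate, and 3% loss to follow-up".
- Per-protocol sample: 159 MIPD and 88 OPD, 247 in total.
- Ratio 0.72, power 80%.

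The attrition figures reproduce the per-protocol sample if conversion applies to the MIPD arm only: 192 × 0.90 × 0.95 × 0.97 = 159.2 and 96 × 0.95 × 0.97 = 88.5.

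**Assumption.** The article gives no number of recoveries. I take all 247 patients as recovering, which is the most favourable case.

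**Step 1: log-rank power (Schoenfeld)**

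Power = Φ(|ln HR| × √(n₁n₂/(n₁+n₂)) − z₁₋α)

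- √(159 × 88/247) = 7.527
- |ln 0.72| = 0.3285
- Product: 2.473

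| One-sided level | Calculation | Power |
|---|---|---|
| 5% | Φ(2.473 − 1.645) | 79.6% |
| 2.5% (two-tailed 0.05) | Φ(2.473 − 1.960) | 69.6% |

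The plan's 80% is reproduced at one-sided 5% and missed by about 10 points at one-sided 2.5%.

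**Step 2: recoveries needed for 80% power**

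D = (z₁₋α + 0.842)² / [p(1−p)(ln HR)²], with p = 159/247 = 0.644

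- One-sided 5%: 249.8, close to the stated 247.
- One-sided 2.5%: about 317.

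**Step 3: ratio detectable with 247 recoveries at one-sided 2.5%**

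exp(−(1.960 + 0.842)/7.527) = 0.689, and 9 × 0.689 = 6.2 days against 9.

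**Step 4: does another method rescue 80% at 2.5%?**

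| Variant | One-sided 5% | One-sided 2.5% |
|---|---|---|
| Freedman formula (range over direction of the ratio) | 75.7% to 82.3% | 64.8% to 72.9% |
| Ratio 6.5/9 instead of 0.72 | 78.9% | 68.8% |
| 90% of patients recover | 75.8% | 65.0% |
| All 288 randomized patients | 83.7% | 74.8% |
| Simulated log-rank, exponential times, 10,000 runs | 78.4% | 67.7% |
| Simulated Gehan-Breslow, same runs | 67.3% | 55.0% |

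None reaches 80% at 2.5%. The first, second, third and fifth rows lie around 80% at one-sided 5%, as the plan's figure does.

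**The case against.** The 5% level is inferred; the article never prints it. The sample-size text specifically calls the recovery test one-sided, whereas the two-tailed sentence is general and follows generic rules for t-tests and chi-square tests. If the specific statement prevails, the test could be one-sided at 5%, the 80% would be right, and only the level would be unstated. The statistical analysis plan could supply it. This reading is possible, but it does not reconcile the text. The two-tailed rule is the only threshold in the analysis section and does not exempt recovery, and the primary outcome's "2.5% one-sided significance level (α") agrees with it. An intended 5% would still contradict the printed threshold, and a later plan does not correct a printed power figure.

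The 70% also depends on the model. If recovery times were not exponential, 6.5 versus 9 days need not mean a ratio of 0.72. With an assumed Weibull shape of 1.15, the ratio would be about 0.69 and power at 2.5% about 80%. However, the article itself states 0.72.

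The Gehan-Breslow figures assume proportional exponential hazards, which favour the log-rank test, and the article chooses between the tests by distribution. They show sensitivity, and the conclusion does not rest on them.

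Finally, the outcome is secondary, and the total of 288 comes from the CCI calculation. The primary inference is therefore unaffected. That limits the reach of the error without removing it.

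**Conclusion.** The concern holds. The stated 80% power for time to functional recovery does not hold at the decision threshold in the article. It corresponds to a one-sided 5% level, twice what two-tailed 0.05 allows in the direction of benefit. At the plan's threshold, log-rank power for a ratio of 0.72 is 69.6%, and 65% to 73% across the Freedman variants.

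This rests on the stated ratio, the stated 159/88 split and every patient recovering. Any censoring lowers the power further. That 5% was the level used is an inference from the arithmetic. The shortfall at 2.5% follows directly from the stated inputs.

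**What to change.** In the Sample size calculation section and in the statistical analysis plan, state the level for time to functional recovery as two-sided 0.05 (one-sided 2.5%), in line with the analysis section and the primary outcome. Then either restate the power as about 70% for a 28% reduction, or say that 80% power applies to a reduction of about 31% (6.2 versus 9 days). The Discussion and Conclusion statements that the trial is powered for this outcome should carry the same figure.

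Declaring one-sided 5% and exempting this outcome from the two-tailed rule would also make the text consistent. It would do so by doubling the false-positive rate on a headline claim, so I do not recommend it.

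The section also names a 2-day effect (7 versus 9 days). The restated power applies only to the 28% reduction and should not be attached to that smaller effect.

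The cost is one sentence, and the stated power falls from 80% to about 70%. No patients are added. With 269 of 288 already randomized when the article was submitted, the practical step is to fix the level in the analysis plan, which is due before database lock.

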## Conclusion

In conclusion, the international randomized controlled, patient-blinded DIPLOMA-2 trial is designed to investigate the non-inferiority of MIPD versus OPD for overall complications (primary endpoint). Secondly, the trial is powered to analyze the superiority of MIPD versus OPD regarding time to functional recovery (secondary endpoint). If successful, the DIPLOMA-2 trial may establish MIPD as the new standard of care for patients undergoing pancreatoduodenectomy in this selected patient population in selected high volume centers following the Miami guidelines. When demonstrating the safety and efficacy of MIPD, the trial may help to expand and standardize the use of MIPD, ultimately leading to better patient outcomes.

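### The 80% power for time to functional recovery is for a 2.5-day effect at an unstated one-sided alpha; it does not match the 2-day effect the protocol assumes or the significance levels it states

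*Protocol article*

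**What the plan says.** All of the power material is in the Sample size calculation section of the protocol article.

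- **Assumed effect:** "we assume MIPD will result in a reduction of 2 days (7 days in the MIPD group versus 9 days in the OPD group".
- **Powered effect:** 159 MIPD and 88 OPD patients in a per-protocol analysis give the stated power. The sample "achieves 80% power to detect a 28% reduction of time to functional recovery (i.e., 6.5 days in the MIPD group", with a hazard ratio of 0.72. The paragraph ends by calling this a median reduction of 2.5 days.
- **Sidedness:** "With a one-sided testing, assuming 5% metastatic disease, 10% conversion rate, and 3% loss to follow-up". No alpha accompanies this. The only one-sided level in the section belongs to the CCI: "2.5% one-sided significance level (α), expected difference of the mean CCI® score in the MIPD and OPD group of 0 points".

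The Statistical analysis section plans a superiority test of this outcome by Gehan-Breslow or log-rank. It then gives a general threshold with no exception for this outcome: "A two-tailed *p*-value < 0.05 will be considered statistically significant". It names the modified intention-to-treat (mITT) set as primary, with converted patients kept in the MIPD group.

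The Discussion says "the trial is also powered to assess superiority of time to functional recovery", and the Conclusion repeats that "the trial is powered to analyze the superiority of MIPD versus OPD regarding time to functional recovery".

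**The concern.** One paragraph contains two effect sizes, and power is given only for the larger. The significance level behind that power is not given, and the two levels that the article does state, one-sided 2.5% and two-tailed 5%, are both stricter than the one needed to reach 80%.

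Time to functional recovery is called the most important secondary outcome, and superiority on it is half of the trial's hypothesis. Two things follow. First, a reader who takes the powered statements at face value will treat a non-significant result as stronger evidence against faster recovery than the design supports. Second, the sidedness is unsettled: a two-sided p-value between 0.05 and 0.10 in favour of MIPD would be a success under one-sided 5% and a failure under the two-tailed rule.

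**Working it through.** **Inputs from the protocol article:** 159 MIPD and 88 OPD; medians 9 versus 6.5 days (HR 0.72), and 9 versus 7 days. The arm sizes reproduce from the stated losses: 192 × 0.95 × 0.90 × 0.97 = 159 and 96 × 0.95 × 0.97 = 88.

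**Assumptions:** every patient reaches functional recovery (no censoring), and the HR equals the ratio of medians. The protocol makes that second step itself, since 6.5/9 = 0.72. It is exact only for exponential times. For 7 versus 9 days the protocol gives no HR; the same step gives 7/9 = 0.778.

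**Formula (Schoenfeld, log-rank):** power = Φ(√(n₁n₂/(n₁+n₂)) × |ln HR| − z).

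√(159 × 88/247) = √56.65 = 7.527.

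- HR 0.72: 7.527 × 0.3285 = 2.472
- HR 0.778: 7.527 × 0.2513 = 1.892

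| Effect | One-sided 5% (z = 1.645) | One-sided 2.5% or two-sided 5% (z = 1.96) |
|---|---|---|
| 9 vs 6.5 days | Φ(0.827) = 79.6% | Φ(0.512) = 69.6% |
| 9 vs 7 days | Φ(0.247) = 59.7% | Φ(−0.068) = 47.3% |

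The plan's own 80% is the top-left cell. Each departure alone costs power: alpha alone takes it to 69.6%, effect alone to 59.7%, and both together to 47.3%.

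**Events needed for 80% at this allocation:** 250 (HR 0.72, one-sided 5%), 318 (HR 0.72, two-sided 5%), 427 (HR 0.778, one-sided 5%) and 542 (HR 0.778, two-sided 5%).

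**Checks on the method.** Simulated log-rank tests on exponential data gave about 67% for 2.5 days and 46 to 47% for 2 days at two-sided 5%. Freedman's formula gave 44.3 to 49.7% for 2 days. The Gehan-Breslow test, which the protocol also allows, gave about 54% and 36% in the same simulations.

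**Sensitivity to the distribution.** With Weibull times of shape k, the HR for 7 versus 9 days is (7/9)^k, so power at two-sided 5% is Φ(1.892k − 1.96):

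- k = 1: 47%
- k = 1.25: 66%
- k = 1.5: 81%
- k = 2: 97%

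The documents do not give k.

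**Analysis set (two-sided 5%).** Removing only the 3% loss leaves 186 and 93, and √(186 × 93/279) = 7.874. Without dilution, power is Φ(7.874 × 0.3285 − 1.96) = 73.5% for 2.5 days and Φ(7.874 × 0.2513 − 1.96) = 50.8% for 2 days. If instead 10% of the MIPD arm convert and recover as OPD, and 5% in each arm are unresected and recover alike, it is about 57% and 39%. Those dilution inputs are assumptions, so the mITT range is roughly 57 to 74% for 2.5 days and 39 to 51% for 2 days.

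**The case against.** **The 80% is not a miscalculation.** A reader might infer an arithmetic error. There is none: it reproduces from its own inputs at one-sided 5%, and the arm sizes reproduce too. The article also discloses that the power is for 6.5 days and never claims 80% for 2 days. This stands. The defect is that the inputs conflict with one another and one of them is missing.

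**The two-tailed rule may not govern this test.** It is a general sentence, the one-sided wording is specific to this outcome, and the primary CCI test is itself one-sided. A reader might infer that 47% is simply the trial's power; it is one cell of the table, reached by changing effect and alpha together and reading the general sentence as controlling. But if the specific wording governs, its alpha is still unstated. The one-sided level that the section does give, 2.5%, leads to the same 70% and 47%, and one-sided 5% still leaves only 60% for the assumed effect.

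**The exponential assumption may be wrong.** Recovery needs five criteria to be met together, so times may well be less dispersed than exponential. At Weibull shape 1.5, power for 2 days would be about 81%. This stands as a limit on the numbers, so calling the test a coin toss would be too strong. The assumption is nevertheless the one the protocol uses to reach 0.72.

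**Analysis set and HR direction.** The article says openly that the power is per protocol and analyses both sets. The lower mITT figures depend on assumptions outside the documents. A reader might infer from 0.72 that MIPD is expected to recover more slowly, because recovery is the event and faster recovery gives an MIPD:OPD ratio of about 9/6.5 = 1.38. The article does not name the reference arm, and power depends only on |ln HR|, so this is a labelling point that changes no figure.

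**Importance.** The outcome is secondary and the 288 comes from the CCI. The primary test is unaffected.

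**Conclusion.** The point holds as an inconsistency in the inputs. The stated 80% belongs to a 2.5-day effect, the per-protocol set and, by inference, one-sided 5%. Against the levels the article states, power for that effect is about 70%. For the 2-day effect it says it assumes, power is about 60% at one-sided 5% and 47% at one-sided 2.5% or two-sided 5%. All of this takes complete recovery, the log-rank test and the protocol's own equation of HR with the ratio of medians. Censoring or the Gehan-Breslow test under proportional hazards would lower the figures; less dispersed recovery times would raise them. On the information given, the unqualified powered statements in the Discussion and Conclusion are not supported. Should-fix: the outcome is the leading secondary one, but it did not set the sample size.

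**What to change.** In the Sample size calculation section, or in the detailed analysis plan due before lock of the 90-day data:

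1. State one effect size for time to functional recovery, with one sidedness and alpha that match the planned test.
2. Name the analysis set to which the power applies, given that mITT is primary.
3. Restate the power and declare the distributional assumption. For example: two-sided 5%, log-rank, 159/88, exponential times, all recovering; about 70% for 9 versus 6.5 days and about 47% for 9 versus 7 days.
4. Give any mITT power as a range under stated assumptions about converted and unresected patients.
5. Name the reference arm for the hazard ratio.
6. Qualify the powered statements in the Discussion and Conclusion accordingly.

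The cost is revised text and less favourable figures. No patients are added and the primary analysis does not change.
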